| **Study Withdrawal Criteria** | Withdrawal refers to a subject no longer receiving the investigational drug treatment in this study (early termination of investigational drug treatment). The circumstances under which a subject withdraws from the study are classified into the following two categories:  **Subject-Initiated Withdrawal**  Subjects may terminate the investigational drug treatment or withdraw from the study at any time. Reasons for withdrawal from the study may include:  –The subject withdraws informed consent;  –The subject is lost to follow-up or has died.   - **Investigator-Initiated Withdrawal** - The investigator may also terminate a subject's participation in the study at any time, based on their professional judgment. - There is evidence of disease progression; - The subject experiences intolerable toxicity leading to drug discontinuation, and recovery has not occurred within 14 days after stopping the drug; - Poor subject compliance, making them unsuitable to continue in the study; - Major protocol deviations that affect drug tolerance and safety evaluation; - The subject is lost to follow-up; - Pregnancy; - Other reasons deemed by the investigator that make the subject unsuitable to continue in the trial. |

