| **Drug Administration Plan** | The dosing phase of this study includes three stages: the single-dose phase, the multiple-dose phase, and the extended dosing phase. The pharmacokinetics of the single-dose and multiple-dose administrations are combined, during which safety, tolerability, and preliminary efficacy are observed.  **1. Single-Dose Phase**  The single-dose escalation phase will begin with the starting dose and proceed in an ascending order from low to high doses, with 3 to 6 subjects enrolled in each dose group. In each dose group, 3 subjects will be enrolled sequentially, and a single dose will be administered on Day 1 (D1) at that dose, followed by a 6-day observation period (D2-D7). Each subject will receive treatment with a single dose.  **2. Multiple-Dose Phase**  After completing the pharmacokinetic blood sampling for the single-dose administration, if the subject is well-tolerated, they will enter the multiple-dose phase, with doses administered on Days 8, 11, and 15. Each subject will receive the same dose as in the single-dose phase, with the dose-limiting toxicity (DLT) observation period defined as the first administration to 25 days after the first dose. Initially, only one subject will be enrolled in each dose group to observe their tolerability and safety within the 25 days following the first dose. Only if this subject does not experience a DLT will the remaining two subjects in the same dose group be allowed to enroll simultaneously.  If none of the 3 subjects in a dose group experience DLT, the trial will proceed to the next dose group. If 1 out of the 3 subjects in a dose group experiences DLT, an additional 3 subjects will be recruited to receive the same dose of the investigational drug, and they will be monitored for DLT occurrence.  If 1 DLT occurs among the 6 subjects, the trial will proceed to the next dose group. If 2 or more DLTs occur among the 3 subjects, or if 2 or more DLTs occur among the 6 subjects, the trial will be reduced to the previous dose group. If the previous dose group has fewer than 6 evaluable subjects, an additional 3 subjects will be enrolled to bring the total number of evaluable subjects to 6. If no more than 1 DLT occurs among the 6 evaluable subjects, the trial will be halted, and that dose group will be declared as the maximum tolerated dose (MTD). If the previous dose group has already reached 6 evaluable subjects, the trial will be halted, and that dose will be declared as the MTD.  During the multiple-dose escalation trial, real-time analysis of the pharmacokinetic (PK) data for the selected dose groups will be conducted to determine whether the drug reaches a saturation state in the body based on PK and pharmacodynamic (PD) indicators.  **3. Extended Treatment Phase**  After completing the single-dose and multiple-dose phases, if the efficacy assessment indicates clinical benefit for the subject, they will enter the extended dosing phase. In the extended dosing phase, treatment may continue according to the original dosing regimen or with adjustments to the dose based on the subject's tolerability and existing clinical results. Each dosing cycle lasts 21 days, with doses administered on Days 1, 4, 8, and 11 of each cycle. The number of extended dosing cycles will vary based on the patient's efficacy; subjects who achieve an objective response rate of partial response (PR) or higher after 6 cycles may continue receiving the treatment until disease progression, while those who do not reach PR will discontinue the treatment. Efficacy and safety data will continue to be collected during the extended dosing phase. |

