## Criteria for Withdrawal from the Study

Participants have the right to withdraw from the study at any stage, and their interests will not be adversely affected by their decision to exit. If a participant requests to withdraw from the trial, study treatment must be discontinued. Additionally, if a participant does not explicitly state their intention to withdraw but ceases to take medication and undergo tests, this will also be considered a withdrawal or dropout.

If a participant decides to withdraw, all observations should be completed and reported as thoroughly as possible before exiting. A full final assessment should be conducted at the time of withdrawal, and the reason for withdrawal must be documented. If a participant withdraws due to adverse events or abnormal laboratory results, relevant details must be recorded in the case report form.

The investigator should consider early termination of the study for a participant in the event of any of the following occurrences:

1. Evidence of disease progression;
2. Appearance of intolerable toxicity leading to discontinuation of the study drug, and failure to recover within 14 days after discontinuation;
3. Poor compliance by the participant, making them unsuitable to continue in the study;
4. Serious violations of the study protocol that affect drug tolerance and safety evaluation;
5. Participant lost to follow-up;
6. Pregnancy;
7. Other reasons deemed by the investigator as making the participant unsuitable to continue in the trial.

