# Study Process

The study is divided into five phases: the screening phase, the single-dose administration phase, the multiple-dose administration phase, the extended dosing phase, and the study conclusion or early termination of participation.

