**Liver Toxicity**

In the event of liver toxicity, additional clinical information should be collected to determine the most likely cause of the observed liver abnormalities. This includes identifying abnormalities in liver function indicators that may be due to other factors, such as concomitant medications, alcoholic and autoimmune hepatitis, tumor metastasis, disease progression, viral hepatitis, cardiovascular disease, and other causes. The following measures should be taken:

Grade 2 Toxicity

- Continue to closely monitor liver function indicators during the Purinostat Mesylate treatment cycle until they return to baseline levels.
- For patients with baseline normal liver function who experience a Grade 2 increase in ALT or AST after treatment, suspend treatment until liver function returns to Grade 1 or below. Upon resuming treatment, the dose should be reduced by one level, and the frequency of liver function monitoring should be increased.

Grade 3 Toxicity

- If ALT or AST> 5×ULN, treatment should be discontinued, and the subject should exit the study. The subject will receive a consultation from a liver disease specialist.
- Closely monitor liver function indicators. If liver function is severely impaired relative to baseline values or reaches the level of severe liver injury, the medication should be discontinued, and supportive care should be strengthened, such as bed rest and close monitoring of liver function indicators, until liver function returns to baseline levels.
- During the process of reducing the dose by one level, if Grade 2 or higher toxicity recurs, treatment should be discontinued, and the subject should exit the study.

Grade 4 Toxicity

- Treatment should be discontinued, and the subject should exit the study. The subject will receive a consultation from a liver disease specialist.

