## Clinical Efficacy Analysis

- Use FAS Analysis:
- Objective Response Rate (ORR): Calculate the ORR and its 95% confidence interval.
- Disease Control Rate (DCR): Calculate the DCR and its 95% confidence interval.
- Progression-Free Survival (PFS): The time from the start of the study to the date of the first recorded progression (PD) or death, whichever occurs first; if no disease progression is observed, the cutoff date should be the date of the last tumor measurement. PFS will be summarized using Kaplan-Meier plots, and the rates of censoring, quartiles, and their 95% confidence intervals will be listed, along with estimates of progression-free survival rates at different time points and their 95% confidence intervals.

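### Under the six-cycle stopping rule, Kaplan-Meier PFS after about D151 rests only on subjects with PR or better, because subjects below PR stop drug, leave the study and are not followed for progression or death

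*Protocol*

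**What the plan says.** **Stopping drug and leaving the study.** The Study Withdrawal Criteria row of the synopsis reads: "Withdrawal refers to a subject no longer receiving the investigational drug treatment in this study (early termination of investigational drug treatment". Section 4.6 lists among its reasons for ending participation: "Appearance of intolerable toxicity leading to discontinuation of the study drug, and failure to recover within 14 days after discontinuation". The liver rules in 8.4 say "treatment should be discontinued, and the subject should exit the study", and the dose-adjustment table in 3.2.5 couples the same two steps for several toxicities.

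**The six-cycle rule.** The Drug Administration Plan row of the synopsis lets subjects with PR or better after 6 extension cycles continue, "while those who do not reach PR will discontinue the treatment". It also states "Each dosing cycle lasts 21 days". The Research design row and section 3.1 describe treatment until progression or intolerable toxicity and mention no six-cycle stop.

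**What is collected after drug stop.** Section 6 names five phases, the last two being "the extended dosing phase, and the study conclusion or early termination of participation". None is a post-treatment follow-up phase. The flowchart ends with a Termination/Early Withdrawal column (±7 days). Section 6.5 puts imaging, bone marrow examination and an efficacy assessment at that visit. After it, only adverse events are followed (8.1.4, 8.2).

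**PFS.** Section 7.5 runs PFS from enrollment to objective progression or death, not limited to time on drug. Section 10.6 censors as follows: "if no disease progression is observed, the cutoff date should be the date of the last tumor measurement". It promises Kaplan-Meier plots, quartiles and PFS rates at different time points, with 95% confidence intervals.

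**The concern.** Kaplan-Meier estimation assumes that censored subjects have the same future risk as those who stay under observation. The six-cycle rule selects on response: at one point in time it stops every subject who is progression-free but below PR, and it keeps those with PR or better. Stopping drug counts as withdrawal and nothing on disease is scheduled after the exit assessment, so the stopped subjects are censored at about that point. From then on the curve follows only the better-responding group, yet it would be read as PFS of all treated subjects. A larger sample does not remove this bias. An analysis plan can change the censoring rule, but it cannot supply progression and death dates that the protocol never collects.

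**Working it through.** **The plan's own figure.** The only size stated is 21-42 subjects: 7 groups × 3 = 21 and 7 × 6 = 42, which reproduces. The protocol gives no PFS rate, median, power or alpha, so the size of the bias can only be illustrated.

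**When the rule takes effect.** The extension starts on D26 and cycles last 21 days. 25 + 6 × 21 = D151, and 151 / 30.4375 = 4.96 months (t0).

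**Assumed inputs (not in the protocol).** Exponential PFS in two classes. A fraction r reaches PR or better, with r = 20%, 30% or 50%. Median PFS is 9, 12 or 18 months for this class and 3, 4 or 6 months for the rest.

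**Formulas.** S_R and S_N are the survival functions with and without PR.
- True PFS: S(t) = r·S_R(t) + (1 − r)·S_N(t).
- Kaplan-Meier limit for t > t0, when all subjects below PR are censored at t0: [r·S_R(t0) + (1 − r)·S_N(t0)] × S_R(t) / S_R(t0).

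**Central case (r = 30%, medians 12 and 4 months, t = 12).**
- S_R(t0) = 0.5^(4.96/12) = 0.751; S_N(t0) = 0.5^(4.96/4) = 0.423.
- PFS at t0: 0.3 × 0.751 + 0.7 × 0.423 = 0.522. Of 42 subjects, about 21.9 are progression-free. About 12.4 of these are below PR and are censored together, which leaves about 9.5.
- True 12-month PFS: 0.3 × 0.5 + 0.7 × 0.125 = 0.2375.
- Kaplan-Meier limit: 0.522 × 0.5 / 0.751 = 0.347.
- Excess: 11.0 points.

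A simulation (n = 42, 4,000 runs) gave 23.6% and 34.7%.

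**Selected cases at 12 months.**

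| PR or better | Median below PR / with PR (months) | True PFS | Kaplan-Meier | Excess (points) |
|---|---|---|---|---|
| 30% | 4 / 12 | 23.75% | 34.7% | 11.0 |
| 30% | 3 / 12 | 19.4% | 29.8% | 10.4 |
| 20% | 4 / 18 (largest) | 22.6% | 38.4% | 15.8 |
| 50% | 6 / 9 (smallest) | 32.3% | 36.2% | 3.9 |

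All 27 combinations (3 × 3 × 3) are biased upward: 3.9 to 15.8 points at 12 months and 3.0 to 12.2 points at 9 months.

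**Toxicity stops.** Adding 10% or 20% early censoring for toxicity, unrelated to prognosis, moved the simulated Kaplan-Meier value only from 34.7% to 34.8% and 35.0%. In this illustration the bias comes from the six-cycle rule.

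**The case against.** Several stronger readings are tempting, and the protocol does not support them.

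- A reader might infer that no disease status is collected once drug stops. That is wrong. Section 6.5 requires imaging, bone marrow examination and an efficacy assessment at the exit visit, and 4.6 asks for a full final assessment. Progression found there is a PFS event. The gap begins after that visit. Section 11.7.1 mentions the last participant's follow-up but defines none.
- A reader might infer that the protocol draws no line between stopping drug and leaving. The withdrawal row goes on to say that subjects may do the one or the other. That hint stands, but no procedure follows from it.
- A reader might infer that the whole PFS curve describes responders. Before about D151, subjects with SD or MR on treatment are at risk too. "Responder" is also inexact, because 7.5 counts MR as objective response in lymphoma and myeloma although MR is below PR.
- A reader might infer that toxicity stops bias PFS. They do so only if related to prognosis, and nothing in the protocol establishes that. The same holds for stops on investigator judgement.

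The strongest objection is that the six-cycle stop stands in one synopsis row and conflicts with the Research design row and 3.1. It also fits acute leukemia poorly, since 14.6 gives no PR category for marrow response. If the stop does not apply, the joint censoring at D151 and all the figures above fall away. What remains is missing follow-up after other stops.

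Precision also matters. In the central case with 42 subjects, Greenwood's formula gives a standard error of 0.347 × √(0.478/21.9 + 0.334/(9.5 × 0.666)) ≈ 0.095, or about ±19 points at 95%. That is wider than the bias. It does not excuse the bias, because the interval is centred on the wrong value. Finally, PFS serves a secondary, preliminary purpose with mainly descriptive analysis.

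**Conclusion.** The concern holds in a limited form. Stopping drug is treated as withdrawal, no progression or survival follow-up is scheduled after the exit assessment, and PFS is still defined to progression or death. Where the six-cycle rule applies, Kaplan-Meier PFS after about D151 reflects only subjects with PR or better and is biased upward. The excess is roughly 4 to 16 points at 12 months, under assumed response rates of 20-50% and assumed medians of 3-6 months without PR and 9-18 months with it. The direction follows whenever subjects below PR progress faster than the others; the size rests entirely on those assumptions. DLT and MTD conclusions are unaffected, and no stated dose decision uses PFS. It is worth correcting because the missing dates cannot be recovered by analysis.

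**What to change.** 1. Reconcile the Drug Administration Plan row of the synopsis with the Research design row and section 3.1 on when treatment ends.
2. In 4.6 and the synopsis, separate stopping study drug from withdrawing from the study.
3. For subjects who stop without progression and have not withdrawn consent, record the date of progression, the start of next anticancer therapy and death. Take these from usual-care records or telephone contact, until progression, death or data cut-off.
4. Use these data in PFS. State one primary rule for progression after new therapy, with the alternative as a sensitivity analysis. Counting such progression mixes in another drug's effect, while censoring at new therapy brings back part of the informative censoring.
5. Where the data are not obtained and the six-cycle stop applies, do not report whole-population Kaplan-Meier PFS beyond about D151.

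Failure to reach PR should not be counted as a PFS event. That would make every progression-free subject with SD or MR fail at D151 and put an artificial drop in the curve.

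The cost is a short amendment, one eCRF page and a small amount of record or telephone follow-up for at most the 42 planned subjects, with no added study procedure. The downside is less regular assessment timing off treatment. The reporting limit in step 5 needs no new data.

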**General flowchart of the study**

|  | **Screening Periods** | **Single administration phase（D1-D7）** | | | **Multiple administration phase（D8-D25）** | | | | **Extended Treatment Phase（D26-）** | | | **Termination / Early Withdrawal from the Trial** |
| --- | --- | --- | --- | --- | --- | --- | --- | --- | --- | --- | --- | --- |
|  | **D-14 - D0** | **D1** | **D2** | **D7** | **D8** | **D11** | **D15** | **D25** | **On the day of drug administration at the beginning of each cycle（D1）** | **On the day of drug administration at the end of each cycle（D11）** | **The last day of each cycle（D21）** |  |
| **Time window** |  |  |  | **±1D** | **±1D** | **±1D** | **±1D** | **±1D** | **±3D** | **±3D** | **±3D** | **±7D** |
| Signed informed consent | **√** |  |  |  |  |  |  |  |  |  |  |  |
| Histopathology or cytopathology | **√** |  |  |  |  |  |  |  |  |  |  |  |
| Demographic information | **√** |  |  |  |  |  |  |  |  |  |  |  |
| Past medical and therapeutic history | **√** |  |  |  |  |  |  |  |  |  |  |  |
| allergic history | **√** |  |  |  |  |  |  |  |  |  |  |  |
| Verification of criteria for admission | **√** |  |  |  |  |  |  |  |  |  |  |  |
| Test drug administration^a^ |  | **√** |  |  | **√**（Administered once on D8, D11, and D15） | | |  | **√**（Administered once on D1, D4, D8, and D11 of each cycle） | |  |  |
| PK collects blood samples |  | **√**（See the PK and biomarker blood sampling workflow diagram） | | | | | |  |  |  |  |  |
| Biomarker collection of blood samples |  | **√**（See the PK and biomarker blood sampling workflow diagram） | | | | | |  |  |  |  |  |
| Vital signs^b^ | **√** | **√**（Checked once at 0.5 hours before administration on D1, and at 0.5 hours, 2 hours, and 24 hours after administration, as well as once on D7） | | | **√**（On D8, D11, and D15, checked once within 0.5 hours before administration and once 2 hours after administration） | | | **√** | **√**（On D1, D4, D8, and D11 of each cycle, each will be checked once within 0.5 hours before administration and once 2 hours after administration） | | **√** | **√** |
| Physical examination | **√** |  | **√** | **√** |  | **√** | **√** | **√** | **√** | **√** | **√** | **√** |
| ECOG score | **√** |  |  |  |  |  |  |  | **√**（pre-administration） |  |  | **√** |
| Urine or blood pregnancy test | **√** |  |  |  |  |  |  |  |  |  |  | **√** |
| Routine blood test^c^ | **√** |  | **√** | **√** |  | **√** | **√** | **√** | **√**^#^ | **√** | **√** | **√** |
| Urine routine^d^ | **√** |  | **√** | **√** |  | **√** | **√** | **√** | **√**^#^ | **√** | **√** | **√** |
| Blood biochemistry^e^ | **√** |  | **√** | **√** |  | **√** | **√** | **√** | **√**^#^ | **√** | **√** | **√** |
| Coagulation^f^ | **√** |  | **√** | **√** |  | **√** | **√** | **√** | **√**^#^ | **√** | **√** | **√** |
| M protein^L^ | **√** |  |  |  |  |  |  | **√** | **√**（pre-administration）^m^ |  |  |  |
| Virological examination^g^ | **√** |  |  |  |  |  |  |  |  |  |  |  |
| 12-lead ECG ^h^ | **√** | **√**（Checked once before administration, and 2 hours, 6 hours after administration, as well as on D2 and D7） | | | √（Checked once 2 hours and 6 hours after administration on D8, and once before administration, as well as 2 hours and 6 hours after administration on D11 and D15, and once on D25） | | | | √（Checked once before administration on D1, D11, and D21, and once 2 hours after administration, with additional checks as deemed necessary by the investigator） | | | **√** |
| Radiographic examination^i^ | **√** |  |  |  |  |  |  | **√** |  |  | **√** | **√** |
| Bone marrow examination^n^ | **√** |  |  |  |  |  |  | **√** |  |  | **√** | **√** |
| Echocardiography^j^ | **√** | △ | △ | △ |  | △ | △ | △ | △ | △ | △ | △ |
| Efficacy evaluation^k^ |  |  |  |  |  |  |  | **√** |  |  | **√** | **√** |
| Compliance evaluation |  | **√** |  |  |  |  |  | **√** |  |  | **√** | **√** |
| Adverse events | **√** | **√** | **√** | **√** | **√** | **√** | **√** | **√** | **√** | **√** | **√** | **√** |
| Concomitant medication | **√** | **√** | **√** | **√** | **√** | **√** | **√** | **√** | **√** | **√** | **√** | **√** |

Note: **√** indicates mandatory items, and **△** indicates optional items based on specific circumstances.

The single-dose phase is from D1 to D7, and the multiple-dose phase is from D8 to D25. The DLT observation period is from D1 to D25. If the participant tolerates the treatment well, they may enter the continuation dosing phase on D26.

**BSA Calculation Formula: Dubois-Dubois formulas，BSA = (W ^0.425^ x H ^0.725^) x 0.007184，Weight (kg), Height (cm); The single and multiple doses are calculated based on the weight at the time of the first administration. In the continuation dosing phase, weight is measured again before each cycle. If the weight changes by 10% or more compared to the initial dosing weight, the dosage for that visit will be based on the actual weight. However, the dosage remains unchanged for each cycle.**

1. Intravenous drip test drug:

- Single administration phase: D1 was administered and observed until D7;
- Multiple administration phase: Administered once on D8, D11, and D15;
- Extended Treatment Phase: Administered once on D1, D4, D8, and D11 of each cycle;

1. Vital signs: including temperature, heart rate, respiratory rate, and blood pressure (systolic and diastolic).

- Single administration phase: Checked once within 0.5 hours before administration, and once at 0.5 hours, 2 hours, and 24 hours after administration;
- Multiple administration phase: On D8, D11, and D15, checked once within 0.5 hours before administration and once 2 hours after administration; checked once on D25;
- Extended Treatment Phase: D1, D4, D8, and D11 of each cycle were examined once within 0.5 h before and 2 h after administration;

1. Complete blood count: red blood cell count, hemoglobin, platelet count, white blood cell count, neutrophil count, lymphocyte count;
2. Urinalysis: urine protein, urine red blood cells, urine white blood cells;
3. Blood biochemistry: blood creatinine, urea, total bilirubin, alanine aminotransferase (ALT), aspartate aminotransferase (AST), alkaline phosphatase, total protein, albumin, electrolytes (K+, Na+, Ca2+, Mg2+, Cl-), total cholesterol, low-density lipoprotein (LDL), high-density lipoprotein (HDL), creatine kinase (CK), creatine kinase isoenzyme (CK-MB), α-hydroxybutyrate dehydrogenase (α-HBDH), lactate dehydrogenase, fasting blood glucose;
4. Coagulation: PT, APTT, TT, FIB;
5. Virology tests: HIV testing (antibodies, antigens), HCV testing (antibodies), HBV testing (HBsAg, HBsAb, HBcAb, HBeAg, HBeAb, HBV-DNA titer).
6. 12-lead ECG: Includes PR intervals, QRS intervals, QT intervals, QTc intervals，

Single administration phase: Checked once before administration on D1 (results from within 5 days prior to D1 may be accepted), and once 2 hours, 6 hours after administration, as well as on D2 and D7;Multiple administration phase: Checked once 2 hours and 6 hours after administration on D8, and once before administration, as well as 2 hours and 6 hours after administration on D11 and D15, and once on D25;Extended Treatment Phase: Checked once before administration on D1, D11, and D21, and once 2 hours after administration; additional checks may be added as deemed necessary by the investigator.

Imaging studies: CT, PET-CT, or whole-body X-ray examinations. Results from screenings conducted within 4 weeks prior do not need to be repeated. During the continuation dosing phase, imaging should be performed once every 2 dosing cycles. If the dosing phase is extended, imaging should occur before the next cycle after the 2nd, 4th, 6th, etc. dosing cycles, with the imaging methods used for evaluating efficacy remaining consistent with the baseline. The examination window is ±3 days. For subjects with leukemia, the primary efficacy evaluation is based on bone marrow smears, and the investigator will determine whether imaging studies are necessary based on clinical circumstances.

Whole-body X-rays include views of the skull, pelvis, femur, humerus, thoracic spine, lumbar spine, and cervical spine.

1. Echocardiography is not a routine examination. It should be performed if the subject experiences symptoms such as precordial pain or palpitations, or if deemed necessary by the investigator.
2. Efficacy assessment: During the continuation dosing phase, for subjects who first achieve disease remission (CR/PR) after the 2nd, 4th, 6th, etc. dosing cycles, efficacy confirmation should be conducted 4 weeks after the initial efficacy assessment.
3. M protein testing is conducted only for patients with multiple myeloma and includes: (1) serum protein electrophoresis (Albumin, Alpha 1, Alpha 2, Beta 1, Beta 2, Gamma, M-spike); (2) immunofixation electrophoresis (IgG, IgA, IgM, light chain types); (3) β2-MG; (4) quantitative serum immunoglobulins (serum IgG, serum IgA, serum IgM, serum kappa light chains, serum lambda light chains, and the kappa/lambda ratio);
4. M protein testing is conducted only at the start of each cycle beginning with the 2nd cycle during the extended dosing phase;
5. Bone marrow examination includes: results from examinations conducted within 4 weeks prior to screening do not need to be repeated. The procedures include: (1) classification of bone marrow cytology smears; (2) bone marrow biopsy with immunohistochemistry; (3) flow cytometry. For leukemia patients, the bone marrow examination is limited to bone marrow smears and flow cytometry;

- The frequency of bone marrow cytology smear classification, bone marrow biopsy with immunohistochemistry, and flow cytometry at the end of multiple dosing and during the extended treatment phase will be determined based on clinical needs.

1. The time window for vital sign checks after administration is±30min.

